**Research Plan**

**Purpose, aim and objectives:**

There are 1.8 billion people between 10-24 years of age, 90% of whom live in low- and middle-income countries(1). Each year, 16 million girls between 15-19 years of age and two million girls under 15 years of age give birth. It is estimated that a lack of access to contraception leads to 7.4 million unintended pregnancies among adolescents, aged 10 to 19 (2, 3). Unintended pregnancies resulted in an estimated 3.2 million unsafe abortions worldwide in 2008, and complications related to pregnancy and childbirth are the leading cause of death for women ages 15-19 (3). There is a high unmet need for sexual and reproductive health (SRH) information and services, for both married and unmarried youth worldwide. However, financial, cultural, social, and legal considerations often impede youth access to the sexual and reproductive health resources that may be available in their communities(4).

While there are efforts in place to make facility-based services and health providers ‘youth-friendly,’ there is a need to strengthen the enabling environment for youth to actually seek care (5). This includes using channels outside of the facility to reach youth with high-quality SRH content and details about the SRH services that are available to them.

Many strategies have relied on creative uses of mass media to engage and educate youth, and the proliferation of mobile technology in recent years and its popularity with young people offers a particularly exciting modality with which to reach this age group. Of the nearly 6 billion mobile phone subscribers worldwide, approximately one-third are under the age of 30 (6). Given the proliferation of mobile phones, they offer the potential of discretely delivering tailored sexual and reproductive health content without stigma or judgment.

The World Health Organization’s Department of Reproductive Health and Research partnered with research partners in Peru and Kenya to initiate the Adolescent/Youth Reproductive Mobile Access and Delivery Initiative for Love and Life Outcomes (ARMADILLO) Study. The goal of ARMADILLO is to develop and evaluate an on-demand system for youth to access and receive SRH information through short message service (SMS, also known as ‘text message’). ARMADILLO is envisioned as a three- stage study (Figure 1): Stage1--developed and tested the message content that will form the ARMADILLO system (A65892 core); Stage 2 (this protocol) —assess the effect of ARMADILLO on knowledge for action, attitudes and self-efficacy using quantitative and qualitative methods; and Stage 3-- a coverage study.

**Stage 1 Summary**

In Stage 1, Kenya and Peru sites both underwent processes to develop and test the messages that would form the ARMADILLO architecture. In Kenya, data collection took place in Mtwapa a peri-urban town in Kilifi County, Kenya. Mtwapa was home to 48,625 people during the 2009 census(7). Mtwapa was selected based on a number of ‘Drop-In Centres’ implemented by the International Centre for Reproductive Health – Kenya (ICRHK, the Kenya site research implementer) - which serve as a combination of health and social centres for adolescents and youth – as well as the strong community ties and partnerships with youth organizations that ICRHK had in this area. In Peru, following strong recommendations from implementing partner Universidad Peruana Cayetano Heredia (UPCH), data collection for the formative phase actually took place in three sites in order to ensure buy-in from across Peru’s distinct geopolitical regions: the coast (Lima), the jungle (Yurimaguas) and the highlands (Ayacucho).

Prior to the start of formative research activities, both researching partners developed draft messages, in close collaboration with local stakeholders. The exact make-up of stakeholder groups varied slightly across sites, however, both sites developed draft messages with a combination of regional/national level stakeholders in adolescent/youth sexual and reproductive health, as well as adolescent/youth involvement themselves.

In Kenya, the resulting messages were categorized by theme (e.g. pregnancy/drug abuse/relationships), while in Peru messages were grouped under overarching questions (e.g. ‘Who am I?’ ‘Who takes care of me?’). The inclusion of youth as equal participants in the identifying of messages topics and content was critical, as youth often identified topics of interest that adult stakeholders had not considered or might not have thought important (for example, youth in Kenya were keen to explore the differences between ‘infatuation’ and ‘love’ as concepts).

In both sites, formative research activities began when the initially-developed messages were vetted for comprehension, relatability, and completeness through a series of Focus Group Discussions with young people aged 15-24 in Kenya and 13-24 in Peru. FGD participants were grouped to be homogenous in sex and age range (15-17 and 18-24 in Kenya, 13-17 and 18-24 in Peru). In all FGDs, youth were asked to provide insight into the following: young people’s use of mobile phones; feedback on a series of the proposed ARMADILLO messages; perceived reactions if siblings, parents and/or significant others were to discover ARMADILLO messages on the phones of a user. In Kenya, following the completion of FGDs, a small survey of possible SRH outcomes was piloted among 250 young people as a way to plan for Stage 2.

Additionally in both sites, a series of FGDs were carried out with parents/caregivers of young people. Parents and caregivers were invited to share their thoughts on where young people learned about SRH issues; how parents handled discussing SRH issues with their children; thoughts on youth access to contraception; and perceived parent reactions if they were to discover their child accessing ARMADILLO messages. In Peru, no survey of possible SRH outcomes was completed, as by the time data collection took place, outcomes for Stage 2 were already decided.

Brief summaries of the formative stage in each site are as follows:

**Kenya:**

A total of 12 FGDs with 95 young people aged 15-24 were conducted, as were an additional four FGDs with a total of 33 parents/caregivers of young people. Findings from these focus groups established that a majority of the youths aged 18-24 had their own personal mobile phones. Meanwhile, adolescents aged 15-17 had phones but mostly used when not in school and shared phones with their siblings and other relatives they lived with. Some even shared with their neighbors and friends especially when doing MPESA (mobile money transfer) transactions. 18-24 year olds reported not to be sharing their phones with anyone save for their confidants whom they trusted.

On getting information about ASRH, it was noted a large majority of young people are afraid to visit health facilities; some said they do not have anyone to turn to for such talks for fear of being labeled ill-mannered boy or girl. Those afraid to visit the health centers opt to look for information online. Youth identified online information as one of their only ‘reliable’ sources of information. SRH information from friends was reported not to be reliable as they equally lacked adequate knowledge to address their concerns. Parents were considered reliable by the youth in giving SRH information; however SRH discussions rarely happened as they were considered culturally inappropriate. Schools were also reliable in giving the SRH knowledge, though the completeness of information was often lacking, leaving young people with many unexplained concerns.

Therefore, when presented with the ARMADILLO platform, a majority of youth agreed they would use it as the information was deemed credible and had undergone due process. It’s was also appreciated for being private and confidential, as young people otherwise lacked such places to obtain information about their SRH. It was also mentioned that young people would be happy with ARMADILLO providing information to SRH concerns in real time.

With regards to concerns about privacy, parents coming across ARMADILLO messages was a concern expressed by some young participants, though a majority didn’t have any problem with their peers accessing their phone’s contents. The general perception was that parents would react differently depending on the age of the one accessing the content: for example, it was reported that those below the age of 18 will be scolded by their parents if seen to be accessing SRH messages while those above 18 years will be considered matured and although their parents won’t be pleased, nothing would be done to them.

By contrast, FGDs with parents and caregivers found them to be in full support of their youth accessing SRH information through text messaging. Parents and caregivers showed strong approval of the service and commended the messages in that they will provide them with a platform to continue with the SRH conversation which at times is difficult to start adding that they would give advice where necessary as well as encourage them to share the information with their younger siblings.

Stage one of the ARMADILLO study established that mobile phones are currently part of young people’s lives and reinforced the fact that sexual and reproductive health messages delivered via text messages from a trusted source will most likely be acceptable to young people owing to its confidential nature.

**Peru**

Stage 1 was carried out in three sites and two steps. The three sites were Lima, the capital city, Yurimaguas in the jungle region, and Ayacucho in the highlands region. For the first step, we worked with local expert committees to develop the potential domains and sub-domains for the ARMADILLO system. These committees included 32 13-17 year olds (22 females and 10 males) and 36 18-24 year olds (3 females and 13 males) and 23 adults from the health and education sectors. Together, these groups developed 7 domains and 25 sub-domains, as well as 2 cross-cutting themes for the ARMADILLO system. Based on these identified domains and sub-domains, the UPCH team developed SMS text messages for each sub-domain. As in Kenya, FGDs were used to validate the SMS text messages with youth. In this step, 104 13-17 year olds (54 females and 50 males) participated. They provided their individual evaluation about how much they liked or didn’t like each text message and their detailed group feedback about each text message (overall content, tone, language).

Additionally, the team also asked adolescent participants about phone sharing and about their perspectives on people finding the ARMADILLO SMS text messages on their phone. About 1 in 4 participants reported sharing their phone with someone else, including their parents, siblings, partners and friends. When asked what they would think about these different groups of people finding their phone and the ARMADILLO messages, unlike youth in Kenya, Peruvian young people stated that it would be fine as long as it is clear that the messages are “public service messages.” It should be clear that they are sent out to many people at once and from a respectable sources. They mentioned that these types of text messages are common in Peru, including for health issues. For example, there have been mass text messages for information of HPV vaccination for girls.

Stage 1 protocols A65893 and A65901 also contain national-level background about both sites, which can be referenced if one wishes to understand how Peru and Kenya were selected as study sites. This Stage 2 protocol builds from the Stage 1 foundation.

**Figure 1**

[figure not shown]

*The ARMADILLO Intervention*

In making decisions about their sexual and reproductive health, young people fall on a spectrum of contraceptive use patterns (8), which range from never having used contraception to being a current user of most effective contraceptive methods (long-acting reversible contraceptive methods).

**Figure 2**

[figure not shown]

This spectrum (Figure 2, above), is fluid, with people likely moving through multiple categories throughout their youth and reproductive years in general. At each point of transition, different strategies may be required to support individuals, should they want to avoid a pregnancy. Access to clear and accurate information, in response to relevant perceptions and/or misconceptions at each transition, is a foundation of all strategies. ARMADILLO serves as a resource of validated SRH information for young people, using a mode of delivery which assures their privacy and comfort.

ARMADILLO consists of an automated, interactive, and on-demand SMS platform that will provide essential facts and address common misconceptions about a full range of SRH issues pertinent to youth, including puberty, relationships, sex, pregnancy, HIV and STIs, and contraception. The ARMADILLO system will be available to users at no charge.

**Study Objectives:**

This research protocol will use an individually randomized design to assess differential learning related to sexual reproductive health and rights compared to those who are asked to learn on their own.

Primary Objective: To determine whether youth given access to ARMADILLO’s targeted SRH information through their mobile phones are more knowledgeable about contraception and better able to dispel contraception myths and misconceptions than those without access to ARMADILLO.

Secondary Objective: To determine whether youth given access to ARMADILLO’s SRH information through their mobile phones retain information on SRHR longer and more accurately than those without access to ARMADILLO.

**Survey of the field:**

Programs using mobile phones have been used in many areas of health care and health promotion globally(9-13). Recent reviews of studies using mobile phones to promote behaviour change have demonstrated mixed to positive effects of such programs(14-17). Studies in the United States, Australia, and South Africa, for example, confirm that text messaging programs for reproductive health can lead to better sexual health and increased use of health services(18, 19). Text messaging programs are a commonly used channel, as texting is the most frequent form of mobile phone communication (20, 21), and is available on every mobile phone regardless of phone model or mobile network provider, with minimal costs per message.

There are numerous projects being implemented globally that leverage mobile technologies for improved youth SRH. Protocol A65893 for the ARMADILLO Study’s formative phase describes in detail some of these projects. As the protocol also highlights, despite enthusiasm for the use of mobile phone technology to reach young people on SRH issues, there is very minimal data to provide insight on the impact of this strategy for increasing knowledge, affecting norms, promoting self-efficacy, and/or improving behaviour. The global health community has issued repeated calls for evidence, particularly around the impact of mobile phone approaches on achieving improved health of populations (22, 23).

The ARMADILLO platform’s structure of on-demand access to SRH information delivered via SMS is but one strategy that capitalizes on young people’s widespread use of mobile and electronic devices to improve information on and access to SRH services. However, ARMADILLO opts to work exclusively with SMS in order to maximize its scalable potential - SMS is a channel for communication available on all mobile phones.

Youth as a group appear to be especially enthusiastic adopters of mobile technology as demonstrated by their comfort using and communicating over various channels on feature and smart phones. Additionally the nature of mobile phone technology itself ensures a level of discretion and privacy that would otherwise not exist when reaching out to this age group on sensitive issues, such as their sexual and reproductive health. Mobile devices can also theoretically transcend gender, marital status, and other demographic information which may otherwise serve as obstacles to accessing SRH information.

The ARMADILLO architecture was developed in each country setting using national and global guidelines around youth sexual and reproductive health, with message wording and content vetted by youth themselves during Stage 1 (Annex 2). This platform is meant to catalyse additional conversations and information- and service-seeking about SRH by providing essential, guidelines- based information which remains available for access at the moment it is needed (and which can be saved for future access).

**Project description:**

***Study Design***

The study uses an individually-randomized, open three-arm comparative design to assess the objectives above. After obtaining written informed consent, individuals randomized to the ‘intervention’ arm of the ARMADILLO trial will receive access to ARMADILLO content over the course of the intervention and will use their mobile phones to access this content on demand. Those randomized to the ‘control’ arm will receive no intervention. Arm 3 will differ by site: in Kenya, those randomized to this ‘contact’ arm will be alerted to various SRH domains (e.g. health topics, including Relationships, Pregnancy, STIs, etc) and be encouraged to learn on their own; in Peru, those randomized to the ‘push’ arm will receive key messages daily with the option to learn more if they wish.

We have elected to include three arms, rather than the traditional ‘intervention’ and ‘control’ arms in an attempt to address lingering questions around the efficacy of informational digital health interventions in different settings. Across all arms, selected SRH outcomes will be assessed via a survey at baseline (prior to the intervention start), at intervention end, and at eight weeks (two months) following the end of the intervention. All outcomes of interest are linked to domains and content from the ARMADILLO system. Control group participants will receive no messaging, only assessments at baseline, and times corresponding to the intervention end and follow-up for the other two groups.

***Data collection methods***

Prior to the start of the study, as part of a finalization of study tools, a number of Focus Group Discussions will be conducted in order to confirm young people’s key myths and misconceptions around contraceptive use, common reasons for not using contraception, as well as build an understanding of where young people access contraception and why. Additionally, in order to streamline the generic study questionnaire (which will assess participant learnings at baseline, end-intervention, and follow-up) to each site as well as ensure comprehension, necessity, and relevance of items for the different age groups being assessed, both Kenya and Peru will conduct a small pilot of the tool among 25-30 youth.

The selected methodology for the effect assessment involves a combination of close-ended surveys and in-depth interviews conducted in person, as well as short, spot assessments via mobile phone. All in-person study activities will take place in a private room at a location and time that is convenient. These rooms allow for both visual and auditory privacy. A project staff member will explain the study activity and answer any questions prior to and/or following completion of the given study activity.

In-person baseline assessment

All participants will complete a baseline, close-ended survey with questions linked to ARMADILLO content. The research team staff will then explain the participant’s expected interaction with the three arms to which they might be randomized and answer any questions. Participants will be told that, should they be randomized to intervention or Arm 3, they can be expect their first message from the system the following day. After the participant leaves, the participant will be randomly assigned to one of the three arms.

Study arms implementation

Generally, messages pushed to phones incur no cost for the recipient. However, the study design requires participants in two of the three arms to send messages as well as receive them – either in response to quiz questions, or in requesting content from ARMADILLO. Message sending does incur charges for the sender (in this case, ARMADILLO study participants). Therefore, both intervention arm and ‘arm 3’ (the format of which varies per site) will be zero-rated, with any SMS charges reversed billed to the study. Participants, during the enrolment process, and periodically during the intervention, will be reminded that any interaction with the study is free. Participants will also be periodically reminded that they can opt out at any time by sending a ‘STOP’ command to a short code.

Despite findings from formative research (see summary of Stage 1 findings above), there is a lingering ethics concern that a person may choose to exclude themselves from a study because their access to messages has somehow compromised their comfort or security. As such, should a member of either SMS-receiving arms indicate via shortcode that they wish to be unenrolled (responding ‘STOP’ to any message received), they will be immediately and automatically unenrolled from the study. Additionally, in order to answer a need ethical/implementation question, they will be sent one follow up message stating:

*‘You are unsubscribed from ARMADILLO and will receive no further contact. If you wish, please tell us why you unsubscribed. Respond 1) don’t like them 2) someone saw them 3) messages don’t relate to me’*

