**Control Arm**

Some participants will be randomly allocated to the control arm. Control arm participants will receive no messages on their phone during the intervention period. Instead, they will only participate in baseline (described above), and end-intervention and follow-up assessments (described below).

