**Figure 4**

**
[figure not shown]
**

Arm 3 and intervention participants in both sites will progress through domains sequentially, based on numbers assigned to each domain (for example, a participant starting at Domain 1 would progress through Domains 2-7 in order in the following weeks). However, participants will be randomized as to which number domain they start with, in order to account for participant recall bias at the end-intervention assessment as a result of having seen one domain 7-8 weeks ago and another one week ago. For example, an intervention/Arm 3 participant may be randomly assigned to start at Domain 3, meaning they would cycle through Domains 4-7 in the following weeks before finishing with Domain 1 and 2. It should be noted that the free airtime intervention and Arm 3 participants receive – meant to subsidize perceived expense for participating in the system – will be credited to users by the study team and does not require negotiation with the mobile network operating companies (MNOs).

End-intervention assessment

Participants from all three arms will be asked to return for an in-person assessment of all outcomes at the end of the intervention. Participants will be able to fill out the end-line survey individually in a private space. Research team members will update participant contact information if necessary and alert participants that they will be invited back for a follow-up assessment in two months

At this visit, a selected sub-sample of intervention participants will also be invited to participate in an in-depth interview. A trained member of the research team will consent these participants and conduct the interview. This interview will provide an opportunity for participants to provide feedback on their experience and opinions using the system. Of particular interest will be recommendations for system improvement; if and with whom they shared messages; perceived ease or difficulty in translating knowledge obtained through ARMADILLO into action (if action was desired or necessary); where they obtained contraception (if applicable); and any recommendations for improving the experience of obtaining contraception.

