***Statistical analysis***All interview data collected as part of the qualitative component of this study will be transcribed in the language it was conducted in and then (if necessary) translated into English verbatim and transferred into an electronic file containing one transcript for each data collection event. The interviewers will use these digital files and interview notes taken during data collection to write summary “topline” reports of study results. Reports will contain information on participants’ experiences and opinions using the system; recommendations for system improvement; if and with whom they shared messages; and perceived ease or difficulty in translating knowledge obtained through ARMADILLO into action (if action was desired or necessary).

The primary outcome, dispelling myths and misconceptions about contraception, will be assessed using an index of contraception myths and misconceptions(30) developed from relevant literature and the planned Focus Group Discussions. Those in the intervention arm are hypothesized to believe fewer contraception myths than those in control arm and Arm 3 and should therefore have a significantly lower index score following the intervention than they did at baseline and compared to endline assessments of the other two groups.

After assessment of the randomization of participants, if there are no differences between arms in terms of sociodemographic characteristics, differences between arms in the contraception myths index score at endline will be assessed using standard methods—comparisons of proportions(chi-square tests) and means (t-tests) between arms and difference-in-difference techniques. If the randomization was not successful, statistical adjustment with multivariable regression will be used to assess intervention impact. It is envisioned that analyses will be conducted as intent-to-treat. Separately, similar secondary analyses will be conducted on knowledge gained and attitudes shifted in other SRH domains assessed, as well as the retention of both primary and secondary outcomes over time (through the follow-up period).

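### A STOP text is written as leaving the study, which conflicts with the all-arm return visit and with intent-to-treat, and can cause differential loss of outcomes in the two SMS arms

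*Protocol*

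**What the plan says.** The rule is in the protocol under Data collection methods, Study arms implementation. It applies "should a member of either SMS-receiving arms indicate via shortcode that they wish to be unenrolled", and its consequence is that "they will be immediately and automatically unenrolled from the study". One automatic message follows. It begins "You are unsubscribed from ARMADILLO and will receive no further contact" and invites a reason: dislike of the messages, someone else having seen them, or lack of relevance. The stated motive is protective, for people who might leave "because their access to messages has somehow compromised their comfort or security". The option is also advertised: "Participants will also be periodically reminded that they can opt out at any time".

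The control arm has no equivalent: "Control arm participants will receive no messages on their phone during the intervention period".

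Outcomes are collected in person. End-intervention assessment says "Participants from all three arms will be asked to return for an in-person assessment of all outcomes", with no exception for STOP senders. Follow-up assessment has the team contact participants again to schedule the final visit. Statistical analysis says "It is envisioned that analyses will be conducted as intent-to-treat".

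Two further places matter. Ethical considerations lets any participant, control included, leave at any time. Study sample size allows up to 20% dropout per site, not split by arm or cause.

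**The concern.** Opting out of messages and withdrawing from the trial are different acts, and the protocol gives them one trigger. A participant who dislikes a text, or whose phone was looked at, has not thereby refused a survey. As the rule is written, the trial nevertheless stops seeking their endline and follow-up outcomes, because inviting them back would break the promise in the auto-reply.

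The primary objective concerns youth given access to ARMADILLO, whether or not they like it, and intent-to-treat needs outcomes on all who were randomised. STOP removes people after randomisation because of how they reacted to what they were allocated. Similar young people in the control arm have nothing to react to and stay. The contrast with control may then compare unlike groups. Missing-data methods in an analysis plan can limit the damage under assumptions, but they cannot recover outcomes that the protocol forbids seeking.

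**Working it through.** **Passages side by side**

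| Place in protocol | What it implies for a STOP sender |
|---|---|
| Study arms implementation, rule | Leaves the study |
| Study arms implementation, auto-reply | Unsubscribed; no further contact |
| End-intervention assessment | Invited back, as all three arms are |
| Follow-up assessment | Must be contacted to be scheduled |
| Statistical analysis | Analysed as randomised |

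The first two rows cannot hold together with the last three.

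**Bias.** The protocol gives no STOP rate, so there is no figure of its own to reproduce. Let s be the share of an SMS arm who STOP and d the mean of STOP senders minus the mean of stayers at endline.

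- Full-arm mean = (1 − s) × stayers' mean + s × STOP senders' mean.
- Observed mean = stayers' mean.
- Size of the bias in a complete-case contrast with control = s × d, if nothing else differs.

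Both s and d are assumptions. In SD units:

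- Low: 0.05 × 0.3 = 0.015 SD.
- High: 0.20 × 0.5 = 0.10 SD.

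For scale, 80% power at two-sided 5% (alpha is not stated; assumed) detects (1.96 + 0.84) × √(2/n) SD. Completers after 20% dropout are 240 × 0.8 = 192 per arm in Peru and 252 × 0.8 = 201.6 in Kenya, which gives 0.286 and 0.279 SD. Against 0.28 SD, the range is 0.015/0.28 = 5% to 0.10/0.28 = 36%.

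On the percentage-point scale, against the planned 10-point change:

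| STOP share | d = 10 points | d = 20 points | d = 30 points |
|---|---|---|---|
| 2% | 0.2 | 0.4 | 0.6 |
| 5% | 0.5 | 1.0 | 1.5 |
| 10% | 1.0 | 2.0 | 3.0 |
| 20% | 2.0 | 4.0 | 6.0 |

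**Type I error.** No SD is stated. Taking the claimed 80% power at 705 per site at face value, 235 per arm × 0.8 = 188 completers implies SD = 0.10 / (2.80 × √(2/188)) = 0.346. The standard error of a contrast is then 0.346 × √(2/188) = 0.0357. With no true effect, a bias of 1, 2 or 4 points raises the two-sided 5% error to about 5.9%, 8.7% or 20.2%.

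**Power.** If STOP exits fall within the 20% allowance, nothing is lost. If they come on top of it, in the SMS arm only, with SD 0.346:

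| Extra STOP loss | Peru (240 per arm) | Kenya (252 per arm) |
|---|---|---|
| 0% | 80.8% | 82.7% |
| 5% | 79.5% | 81.4% |
| 10% | 78.1% | 80.0% |
| 20% | 74.6% | 76.6% |

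The 705 itself does not reproduce as a comparison of 55% with 45%: that needs 392 per arm, 392/0.8 = 490 after dropout, and 1,470 per site. That is a separate matter. Here 705 serves only to back out a working SD.

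**The case against.** The strongest reply is that the rule is a deliberate safeguard. It defines STOP as a wish to leave, cites comfort and security, and Peru enrols 13–17 year olds. Contacting someone again whose messages were seen is not a trivial cost. This stands, and it shapes the fix. It does not explain why a reaction to messages must also end survey participation when full withdrawal is available to everyone separately.

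It can also be said that the auto-reply speaks of being unsubscribed from ARMADILLO, that all arms are to be asked back, and that the consent forms, not shown here, may separate messages from surveys. A reader might infer that STOP senders will certainly get no survey. The document does not settle that. It contains two incompatible statements, and the general invitation does not cancel the specific promise of no contact.

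Other stronger readings also go too far:

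- **That outcomes go missing only in the SMS arms.** This is true of STOP-caused loss alone. Anyone may leave, and dropout is expected in each site. Under Incentives, quiz airtime meant to limit loss goes only to the SMS arms, so loss in control could even be higher.
- **That loss is tied to the myths score and favours the SMS arms.** The listed reasons concern the messages, not knowledge. Someone who finds them irrelevant may already know the material, which would reverse the bias.
- **That all contrasts suffer equally.** The intervention arm and Arm 3 share the STOP rule, so their contrast is less exposed. It is not immune, because STOP rates may differ between them; Peru's push arm, for instance, also has a weekly opt-out.
- **That the endline gap is the whole bias.** Difference-in-difference is among the planned methods. Under it, a stable gap already present at baseline cancels, and only a gap in change matters.

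**Conclusion.** The point holds as a conflict in the protocol with a real but unquantified risk of bias. The STOP rule, the all-arm return visit and the envisioned intent-to-treat analysis must be reconciled. As written, STOP can cause differential missing outcomes after randomisation, mainly in contrasts with control.

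The 0.015–0.10 SD range rests wholly on an assumed 5–20% STOP share, an assumed 0.3–0.5 SD gap and a complete-case analysis. Its upper end needs a STOP share equal to the entire all-cause dropout allowance. If STOP is rare, the bias is small. Power is a minor issue.

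A reader might conclude that the rule defeats intent-to-treat. The document does not support that: nobody is reallocated, baseline data exist for all, and handling of missing data may be set out in an analysis plan not shown. The rule weakens the analysis by an amount that cannot be known in advance. It should be settled before enrolment, since outcomes lost after a promise of no contact cannot be sought later.

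**What to change.** Reword the rule in Study arms implementation so that:

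- STOP ends all ARMADILLO messages at once, as now;
- the participant remains in the randomised arm and is invited to the in-person endline and follow-up surveys, by a contact route agreed at consent;
- withdrawal from the study as a whole is a separate act, recorded separately and available at any time.

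Make End-intervention assessment and Follow-up assessment say the same. Change the auto-reply to state that no further ARMADILLO messages will be sent and how to leave the study altogether. Report STOP counts and survey completion by arm.

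The cost is wording in the protocol, the consent forms and one automatic message. The downside is that some invitations reach people who opted out, including those who report that someone saw their messages. The route must therefore be one the participant chose, and the ethics committee must accept the wording.
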